### Exclusion criteria

Patients will be excluded if they have a previous history of pelvic radiotherapy, double primary cancer other than skin or thyroid cancer, or severe comorbidity, or if they had participated in another clinical trial within 1 month.

### Dropout criteria

Patients who withdraw consent will be dropped out of the study, as will patients with any medical issues or unexpected toxicities, defined as grade ≥ 3 toxicities based on Common Terminology Criteria for Adverse Events (CTCAE) v5.0 occurring during treatment.

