### Data collection and follow-up period

The primary endpoint will be the incidence of acute RIE, and the secondary endpoints will be chronic RIE and toxicities due to probiotics. Patient enrollment and treatment is expected to be completed within 2 years. Patient data on endpoints will be collected before the start of radiotherapy, every week during radiotherapy, every 3 months for the first 2 years after radiotherapy, and every 6 months subsequently for up to 5 years after radiotherapy (Fig. 2). All toxicities will be graded using CTCAE v5.0. The trial design and protocol adhere to the Recommendations for Interventional Trials (SPIRIT) criteria. The SPIRIT checklist and figure can be found in Supplemental Table S1.

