### Sample size and statistical analysis

Two proportion test in Power Analysis and Sample Size Software 2018 (NCSS, LLC. Kaysville, Utah, USA) was utilized to estimate the sample size. Based on the assumption that 30% of the patients in the placebo group and 15% of the patients in the probiotics group will experience grade ≥ 2 acute toxicities, 118 patients per group will be required to show a significant effect based on an alpha value of 0.05 and a beta of 0.2. Assuming a 5% dropout rate, 124 patients per group will be required (total, 248 patients).

Acute toxicities will be analyzed in the intention to treat population, with categorical variables in the two groups compared by the Chi-Square or Fisher’s exact test. To find the other confounding factors for RIE, univariate and multivariate logistic regression for acute toxicity will be performed. The times from the start of radiotherapy to acute grade ≥ 2 toxicities and to any chronic toxicities will be calculated using the Kaplan-Meier method and compared in the two groups using the log-rank test to compare survival curves between two groups. In the whole population, multivariate analysis, Cox proportional hazard model will be utilized to find the significant factor for the incidence of RIE in addition to the use of probiotics. Factors with *p* ≤ 0.2 in log-rank test will be entered in multivariate analysis. Descriptive statistics of all analyzed parameters will be provided, whenever appropriate.

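### The dropout rule takes patients with grade ≥ 3 toxicity out of the study, which conflicts with the intention-to-treat analysis and the 5-year endpoint follow-up

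*Protocol article*

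**What the plan says.** All references are to the protocol article.

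- **Dropout criteria.** "Patients who withdraw consent will be dropped out of the study, as will patients with any medical issues or unexpected toxicities". The sentence goes on to define these by severity, as grade ≥ 3 "toxicities based on Common Terminology Criteria for Adverse Events (CTCAE) v5.0 occurring during treatment". Bowel toxicity is not excepted, and such patients are handled like those who withdraw consent.
- **Data collection and follow-up period.** On endpoints, this section states: "The primary endpoint will be the incidence of acute RIE, and the secondary endpoints will be chronic RIE and toxicities due to probiotics". Endpoint data are to be collected before radiotherapy, weekly during it, every 3 months for 2 years and then every 6 months up to 5 years, with all toxicities graded by CTCAE v5.0. The same part of the article (after Fig. 2) sets an interim toxicity rule: stop the trial if the between-group odds ratio for acute toxicity above grade 2 exceeds 2.
- **Sample size and statistical analysis.** The planned event is acute toxicity of grade ≥ 2, assumed in "30% of the patients in the placebo group and 15% of the patients in the probiotics group". "Acute toxicities will be analyzed in the intention to treat population". Time to acute grade ≥ 2 toxicity and time to any chronic toxicity are analysed by Kaplan-Meier and log-rank. On losses: "Assuming a 5% dropout rate, 124 patients per group will be required (total, 248 patients").
- **Discussion.** Acute RIE is described as something that can go on to late RIE.

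Nowhere does the article say that dropped patients stay under assessment, or how they are counted.

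**The concern.** The rule merges two different things: stopping study product and leaving the study. Grade ≥ 3 RIE is the severe part of the grade ≥ 2 event on which the trial is sized, so an outcome of interest becomes a reason for removal. An intention-to-treat analysis needs outcomes on everyone randomised, and a rule that ends participation stops the collection of those outcomes.

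At stake are the completeness of the primary outcome, the validity of the chronic RIE comparison, and the safety record in the patients with the most serious toxicity. If probiotics reduce severe RIE, the loss would also differ between arms. An analysis plan cannot recover data that the protocol has stopped collecting.

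**Working it through.** **1. The plan's own figure.** Inputs: 30% and 15%, and "based on an alpha value of 0.05 and a beta of 0.2". Sidedness is not stated; two-sided is assumed because it reproduces the result. With unpooled variance:

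n = (1.96 + 0.8416)² × (0.30×0.70 + 0.15×0.85) / 0.15² = 117.7, so 118 per group.

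This matches "118 patients per group will be required to show a significant effect". For dropout, 118 × 1.05 = 123.9 gives 124, while 118 / 0.95 = 124.2 would give 125. The one-patient difference is immaterial, so the sample-size arithmetic is not the problem. Inflating for dropout does suggest that dropped patients are expected to contribute nothing to the analysis.

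**2. What the rule does to each type of patient, read literally.**

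| Patient | Primary outcome (acute RIE) | Chronic RIE and safety follow-up |
|---|---|---|
| Grade ≥ 3 RIE | Event already graded when dropout is triggered; article does not say how it is counted | Lost |
| Non-bowel grade ≥ 3 toxicity or medical issue before RIE | Incomplete: RIE not observed afterwards | Lost |

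The first row makes censoring in the chronic RIE analysis potentially informative: those censored are the severe acute cases, whom the Discussion regards as able to go on to late RIE. The interim rule counts toxicity above grade 2, that is, the same events that trigger removal.

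**3. Loss before RIE is observed (second row).** The article gives no rate. Suppose a fraction h of each arm is lost this way and left out of the analysis. Normal-approximation power (pooled variance), starting from 124 per arm, is 0.81 with no loss and 0.79, 0.77, 0.72 and 0.66 for h = 5%, 10%, 20% and 30%.

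**4. Conditional calculation: grade ≥ 3 RIE cases not counted.** Let s be the share of grade ≥ 2 events that are grade ≥ 3, equal in both arms. The article gives no value, so a range is shown.

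- Loss per arm: 0.30s (placebo) and 0.15s (probiotics), so twice as frequent on placebo. The average is 0.225s.
- The 5% allowance is used up when 0.225s = 0.05, that is s = 0.05 / 0.225 = 22%.
- Rates after exclusion: p(1 − s) / (1 − ps), with n per arm reduced to 124(1 − ps).
- Rates if coded as non-events: p(1 − s), with n = 124.

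Exact power of the uncorrected chi-square test, against 0.820 with no loss at 124 per arm:

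| s | Loss, placebo / probiotics | Rates after exclusion | Power, excluded | Power, non-events |
|---|---|---|---|---|
| 10% | 3.0% / 1.5% | 27.8% / 13.7% | 0.784 | 0.768 |
| 20% | 6.0% / 3.0% | 25.5% / 12.4% | 0.745 | 0.707 |
| 1/3 | 10.0% / 5.0% | 22.2% / 10.5% | 0.678 | 0.610 |
| 50% | 15.0% / 7.5% | 17.6% / 8.1% | 0.577 | 0.470 |

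**5. Direction of any bias.** After equal-share exclusion the odds in each arm are p(1 − s) / (1 − p), so the factor (1 − s) cancels. The odds ratio stays at (0.15/0.85) / (0.30/0.70) = 0.412 for every s. At s = 1/3 the risk ratio moves from 0.50 to 0.105 / 0.222 = 0.474, away from 1, and the risk difference shrinks from 15.0 to 11.7 points. If the cases are coded as non-events at s = 1/3, the rates are 20% and 10%: the odds ratio is (0.10/0.90) / (0.20/0.80) = 0.444 and the risk ratio stays at 0.50.

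**The case against.** **The severe events need not be lost.** A grade ≥ 3 RIE must be graded before it can trigger dropout, so the primary event is already on record. An intention-to-treat count and a time-to-first-event analysis could both include it, and the interim rule shows that the trial means to count such events. This stands. It makes the table in step 4 conditional, and it leaves the two follow-up harms untouched.

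**Unexpected toxicity might not include RIE.** The Background puts acute RIE at 60–80% of patients, so an investigator could regard it as expected. Some ambiguity remains, but the sentence defines the term by grade alone. Even on this reading, non-bowel toxicities and medical issues still remove patients.

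**The article condenses protocol version 1.6.** The full text may keep dropped patients in follow-up. That is possible, but the article states the removal rule outright, and it conflicts with other text in the same article.

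**A stronger reading is tempting:** that the rule biases the acute comparison towards the null. The document does not support this as a general claim. Under equal-share exclusion the odds ratio is unchanged and the risk ratio moves away from 1; only the risk difference shrinks. Bias towards the null on the odds ratio needs a further assumption, such as coding the cases as non-events or a benefit concentrated in grade ≥ 3 events. Nor does the article say that severe acute RIE predicts chronic RIE, or how common non-bowel grade ≥ 3 toxicity is.

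**Conclusion.** The contradiction is real. As written, the rule ends participation for patients whom the analysis and follow-up sections need. The firm harms are an incomplete primary outcome in patients dropped before RIE appears, and loss of severe acute cases from chronic RIE and safety follow-up. The resulting censoring is potentially informative and, if probiotics work, differs by arm. The article gives no rates from which to size these harms.

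The power loss for the primary test (0.82 to 0.78–0.58 if cases are excluded, 0.77–0.47 if coded as non-events) rests on two assumptions: a grade ≥ 3 share of 10% to 50%, and not counting events that have already been graded. On the first assumption alone, dropout by this route exceeds the 5% allowance once the share passes about 22%, before consent withdrawals or other toxicities. Confidence is high on the contradiction and the lost follow-up, and lower on any damage to the primary test.

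**What to change.** Reconcile the Dropout criteria, the follow-up schedule, the interim toxicity rule and the statistical analysis section:

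- Limit the dropout rule to study product, leaving the clinical criterion as the investigators set it.
- State that only withdrawal of consent to follow-up ends data collection.
- Keep all other patients on the existing assessment schedule.
- Count grade ≥ 3 RIE as a primary-endpoint event.
- Analyse all randomised patients in their assigned group.
- For patients already dropped, resume follow-up or retrieve outcomes where consent allows, and report the losses by arm and reason.

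The cost is a short amendment and continued data entry at visits already scheduled. Recruitment began in June 2019 and was expected to finish by June 2021, so some data from patients dropped early may not be recoverable.

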### Treatment implementation

Patients allocated to the probiotics group will be administered two Biscanen capsules (*Bacillus licheniformis* 250 mg containing 250 million colony forming units) three times per day, starting 2 weeks before the initial day of pelvic radiotherapy to the final day of radiotherapy. Patients in the placebo group will be administered placebo pills according to the same schedule.

Prior to radiotherapy, all patients will undergo enhanced computed tomography (CT) scans at 2.5 mm thickness. Participants should be relaxed and in a supine position facilitated by immobilization devices. Simulation CT images will be fused with the results of diagnostic magnetic resonance imaging or positron emission tomography-computed tomography in patients who require delineation of the prostate or gross target volume. Clinical target volume (CTV) will include pelvic regional nodal areas, based on the Asan Medical Center protocol for each tumor type. The upper margin for pelvic radiotherapy will be the junction of the 4th and 5th lumbar spine. The planning target volume (PTV) will include the CTV with 3–10 mm margins. Organs at risk, including the small bowel, large bowel, bladder, rectum, and femoral head, will be delineated according to the guidelines of the Radiation Therapy Oncology Group.

All patients will receive intensity modulated radiotherapy (IMRT) with the PTV required to be irradiated with ≥95% of the prescribed dose. Dose constraints will include the following: 1) 30% of the entire volume of the bowels (small and large) must not receive more than 40 Gy irradiation; 2) 60% of the volume of the rectum must receive ≤40 Gy; 3) 35% of the bladder volume must receive ≤45 Gy (except in patients with bladder cancer); and 4) 15% of the femoral head volume must receive < 35 Gy. Quality assurance will be performed before radiotherapy in all patients. During each treatment, cone-beam CT will be performed for image guidance. Radiotherapy will be scheduled to begin within 10 days after CT simulation, with the total radiotherapy period not exceeding 10 weeks.

### Data collection and follow-up period

The primary endpoint will be the incidence of acute RIE, and the secondary endpoints will be chronic RIE and toxicities due to probiotics. Patient enrollment and treatment is expected to be completed within 2 years. Patient data on endpoints will be collected before the start of radiotherapy, every week during radiotherapy, every 3 months for the first 2 years after radiotherapy, and every 6 months subsequently for up to 5 years after radiotherapy (Fig. 2). All toxicities will be graded using CTCAE v5.0. The trial design and protocol adhere to the Recommendations for Interventional Trials (SPIRIT) criteria. The SPIRIT checklist and figure can be found in Supplemental Table S1.

**Fig. 2 Fig2:**
[figure not shown]
Intervention and assessment schedule for the PREP trial according to the recommendations for interventional trials (SPIRIT)

There will be interim analysis for toxicities but not for efficacy at the timing when 50% of target subjects will be enrolled. The trial will be terminated early if the odds ratio of acute toxicities grade over 2 is more than 2 between the two groups. To protect patient data, each patient will be assigned a separate identification code. All data will be stored in password-accessible files, available only to investigators. All data will be deleted 3 years after the end of the study.

### Sample size and statistical analysis

Two proportion test in Power Analysis and Sample Size Software 2018 (NCSS, LLC. Kaysville, Utah, USA) was utilized to estimate the sample size. Based on the assumption that 30% of the patients in the placebo group and 15% of the patients in the probiotics group will experience grade ≥ 2 acute toxicities, 118 patients per group will be required to show a significant effect based on an alpha value of 0.05 and a beta of 0.2. Assuming a 5% dropout rate, 124 patients per group will be required (total, 248 patients).

Acute toxicities will be analyzed in the intention to treat population, with categorical variables in the two groups compared by the Chi-Square or Fisher’s exact test. To find the other confounding factors for RIE, univariate and multivariate logistic regression for acute toxicity will be performed. The times from the start of radiotherapy to acute grade ≥ 2 toxicities and to any chronic toxicities will be calculated using the Kaplan-Meier method and compared in the two groups using the log-rank test to compare survival curves between two groups. In the whole population, multivariate analysis, Cox proportional hazard model will be utilized to find the significant factor for the incidence of RIE in addition to the use of probiotics. Factors with *p* ≤ 0.2 in log-rank test will be entered in multivariate analysis. Descriptive statistics of all analyzed parameters will be provided, whenever appropriate.

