## Methods/design

### Study aim and design

The PREP study is a prospective, double-blinded, placebo-controlled, randomized trial ongoing at Asan Medical Center, Seoul, Korea. The primary aim of the study is to investigate the efficacy of probiotics, starting 2 weeks before radiotherapy, to prevent acute RIE in patients being treated with pelvic radiotherapy for gynecologic or urologic malignancies. Secondary aims include evaluations of the effects of probiotics on the incidence of chronic RIE and the safety of probiotics in patients with gynecologic or urologic cancer.

The design of the PREP trial is illustrated in Fig. 1. Patients diagnosed with gynecologic or urologic malignancies and scheduled to undergo pelvic radiotherapy will be screened and provided with an appropriate explanation about the PREP trial. Written informed consent will be obtained by radiation oncologists from patients who elect to participate in the study. After stratification by sex, participants will be randomly assigned 1:1 to the probiotics or placebo group using blocked randomization. Sex will be the single stratification factor, as patients with gynecologic malignancies have a greater tendency to require concurrent chemoradiotherapy, which affects the incidence of RIE. The block size and sequence for randomization will vary. The randomization sequence will be generated by a central web-based computer so that allocation will be concealed from the primary investigator who enrolls the patients. Neither participants nor physicians will be aware of their group assignments.

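### Randomisation is stratified by sex, but the stated chi-square/Fisher and log-rank tests do not use sex: valid and mildly conservative, and free to improve

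*Protocol article*

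**What the plan says.** On design, the Protocol article (*Study aim and design*) states: "After stratification by sex, participants will be randomly assigned 1:1 to the probiotics or placebo group using blocked randomization". Sex is the only stratification factor, and the reason given is that "patients with gynecologic malignancies have a greater tendency to require concurrent chemoradiotherapy, which affects the incidence of RIE". The protocol therefore treats sex as prognostic for its own primary outcome.

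On the endpoint (*Data collection and follow-up period*): "The primary endpoint will be the incidence of acute RIE". This is a proportion.

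On analysis (*Sample size and statistical analysis*):
- Acute toxicities are analysed by intention to treat, "with categorical variables in the two groups compared by the Chi-Square or" Fisher's exact test.
- Times to acute grade ≥ 2 toxicity and to any chronic toxicity are "compared in the two groups using the log-rank test to compare survival curves between two groups".
- Logistic models serve a different purpose: "To find the other confounding factors for RIE, univariate and multivariate logistic regression for acute toxicity will be performed".
- For the Cox analysis, factors are screened. Those with p ≤ "0.2 in log-rank test will be entered in multivariate analysis".

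Sex is not named in any of these analyses.

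**The concern.** Blocking within sex keeps the arms balanced on sex, so differences in risk between men and women no longer add to the random error of the treatment comparison. A test that ignores sex still counts that variation in its variance. If sex is prognostic, as the protocol says, the unstratified standard error is somewhat too large, the p-value is on average somewhat too big and some power may be lost.

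The planned regressions do not settle this. They are described as a search for other factors. The only entry rule stated is a p-value screen, so nothing guarantees a sex-adjusted treatment effect. The design and the analysis do not match, and what is at stake is precision.

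**Working it through.** **1. The plan's own figure.** Inputs from *Sample size and statistical analysis*: 30% vs 15%, alpha 0.05, beta 0.2. Two-sided, unpooled variance:

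n = (1.960 + 0.842)² × (0.30×0.70 + 0.15×0.85) / 0.15² = 7.849 × 0.3375 / 0.0225 = 117.7, so 118 per group. This reproduces the stated 118. Dropout: 118 × 1.05 = 123.9, so 124 (118/0.95 = 124.2). Exact power of the unstratified, uncorrected chi-square test is 79.8% at 118 and 82.0% at 124 per group. The sample size was planned for an unadjusted comparison and holds for one.

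**2. Assumed inputs.** The article gives no sex mix and no rates by sex. Assumed: share of women w from 50% to 80%; placebo risk higher in women by δ = 0 to 30 points, with 40 points as an extreme; overall rates held at 30% vs 15%; common odds ratio across sexes; exact 1:1 balance within sex.

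**3. How much the variance is overstated when there is no treatment effect.** With overall risk p = 0.30:

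p(1−p) = (average within-sex variance) + w(1−w)δ²

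The unstratified test uses 0.30 × 0.70 = 0.21. The comparison actually carries 0.21 − w(1−w)δ². The SE ratio is r = √{0.21 / [0.21 − w(1−w)δ²]}, and the true size is about 2[1 − Φ(1.96 r)].

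| w | δ | w(1−w)δ² | r | size |
|---|---|---|---|---|
| 0.5 | 0.10 | 0.0025 | 1.006 | 4.9% |
| 0.5 | 0.20 | 0.0100 | 1.025 | 4.5% |
| 0.5 | 0.30 | 0.0225 | 1.058 | 3.8% |
| 0.8 | 0.20 | 0.0064 | 1.016 | 4.7% |
| 0.8 | 0.30 | 0.0144 | 1.036 | 4.2% |
| 0.5 | 0.40 | 0.0400 | 1.111 | 2.9% |

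**4. Simulation.** Uncorrected chi-square against Cochran-Mantel-Haenszel (CMH) stratified by sex, two-sided 0.05, at least 200,000 trials per scenario (simulation standard error of a power figure at most about 0.1 point).

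118 per arm:

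| women | δ (points) | chi-square size | power, chi-square | power, CMH |
|---|---|---|---|---|
| 50% | 0 | 5.1% | 79.8% | 79.8% |
| 50% | 10 | 4.9% | 79.8% | 80.1% |
| 50% | 20 | 4.5% | 80.3% | 81.2% |
| 50% | 30 | 3.9% | 80.9% | 83.0% |
| 70% | 10 | 4.9% | 79.8% | 80.0% |
| 70% | 20 | 4.6% | 80.2% | 80.9% |
| 70% | 30 | 4.0% | 80.6% | 82.3% |

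124 per arm, power for chi-square vs CMH:
- 50% women: 82.5% vs 83.1% (δ = 20), 83.2% vs 85.0% (δ = 30).
- 70% women: 82.1% vs 81.9% (δ = 10), 82.5% vs 82.9% (δ = 20), 82.9% vs 84.2% (δ = 30).
- 80% women: 81.9% vs 81.7% (δ = 10), 82.3% vs 82.5% (δ = 20), 82.5% vs 83.4% (δ = 30).
- No sex difference: CMH is about 0.5 point lower (82.0% vs 81.5%), which is the lower end of the range.

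CMH size stayed at about 4.9–5.1% throughout. At 124 per arm and 50% women, chi-square size was 4.4% at δ = 20 and 3.7% at δ = 30.

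**5. Extreme case.** Placebo risks of 50% in women and 10% in men, with equal numbers of each, 124 per arm: chi-square size 2.9%, power 83.9%; CMH 5.1% and 87.2%. At 118 per arm power is 81.8% vs 85.6%. The gain is 3–4 points.

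**6. Not computed.** The log-rank loss was not quantified, because the article gives no distribution of event times.

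**The case against.** The strongest reply is that nothing here is invalid. An unstratified test after stratified allocation holds its type I error; it errs only towards caution. A reader might infer that the confidence intervals are wrong in a way that endangers the conclusion, or that the trial is underpowered. Neither follows. Over the range up to 30 points the SE is at most about 5% too large, and chi-square power stays at about 80% at 118 per arm and about 82–83% at 124. This part of the reply stands in full.

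A second reply is that the gain depends on figures the article does not give. Equal numbers of men and women give the largest gain of the mixes tried, and nothing in the article supports a fivefold difference in risk by sex. With a 10-point difference CMH gains almost nothing at 118 per arm and is marginally worse at 124. This also stands.

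A reader might also infer that chance imbalance in chemotherapy within a sex is left in the primary estimate as a defect. It is ordinary chance error, already covered by the unadjusted variance, and stratifying the test by sex would not remove it. It is no part of this point.

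Finally, the article condenses a fuller protocol, which may specify stratification or fixed covariates. That weighs most for the log-rank test, where only the word stratified is absent. It weighs less for acute toxicity, where a specific unstratified test is named. The regression models are a partial answer, but they do not commit to including sex.

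**Conclusion.** The mismatch is real and small. The article randomises within sex because it expects sex to matter for RIE, then names tests that do not use sex and regressions that do not fix it as a covariate.

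Assuming 30% vs 15% overall, a common odds ratio and 50–80% women, the unstratified chi-square has a true size of about 4.4–5.1% for sex differences up to 20 points and 3.7–4.3% at 30 points. Stratifying changes power by about −0.5 to +1 point up to 20 points and by about +1 to +2 points at 30 points. It reaches 3–4 points only in the extreme 50%/10% case with equal numbers of each sex. False positives are not inflated, and 118 per group (124 with dropout) stands. For the log-rank test the same reasoning gives the direction, but no size can be stated. This is a point of efficiency and consistency with the design, not a threat to the trial's conclusion.

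**What to change.** In *Sample size and statistical analysis*:
- Name a Cochran-Mantel-Haenszel test stratified by sex as the primary comparison of acute RIE, reported with a sex-stratified risk difference or common odds ratio and its 95% CI. The risk difference stays on the scale of the planning rates.
- Stratify the log-rank tests by sex.
- State that treatment and sex are kept in the logistic and Cox models whatever the p ≤ 0.2 screen shows.

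The cost is a sentence or two. Sex is already recorded for randomisation, so no new data are needed and the sample size does not change. If sex turns out not to be prognostic, the price is at most about half a point of power. The change should be made before unblinding, so that the adjusted result cannot appear to have been chosen afterwards.

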### Inclusion criteria

Patients will be included if they [1] have histologically proven malignancies of the uterus, ovary, vagina, vulva, bladder, urethra, or prostate [2]; are aged > 20 years [3]; have an Eastern Cooperative Oncology Group performance score of 0–2 [4]; have an adequate hematologic condition within 6 months after enrollment, defined as absolute neutrophil count ≥1500 cells/mm^3^, platelet count ≥50,000 cells/mm^3^, and hemoglobin ≥8.0 g/dl [5]; have appropriate kidney function within 6 months after enrollment, defined as creatinine < 2.0 ng/dL; and [6] have appropriate liver function within 6 month after enrollment, defined as total bilirubin < 1.5 times the maximum normal value and alanine aminotransferase and aspartate aminotransferase < 2.5 times the maximum normal value.

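### Kaplan-Meier for time to chronic toxicity does not estimate the incidence of chronic radiation induced enteropathy (RIE), which is the stated secondary aim, once patients die free of it

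*Protocol article*

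**What the plan says.** - **Aim.** Under Study aim and design, the protocol article lists among its secondary aims "evaluations of the effects of probiotics on the incidence of chronic RIE". The section Data collection and follow-up period repeats this as an endpoint: "the secondary endpoints will be chronic RIE and toxicities due to probiotics".
- **Method.** Under Sample size and statistical analysis, times counted from radiotherapy start "to any chronic toxicities will be calculated using the Kaplan-Meier method and compared in the two groups using the log-rank test". For the whole population, a "Cox proportional hazard model will be utilized to find the significant factor for the incidence of RIE".
- **Follow-up.** Endpoint data are collected at 3-month intervals for 2 years and then "every 6 months subsequently for up to 5 years after radiotherapy".
- **Population.** Patients have "histologically proven malignancies of the uterus, ovary, vagina, vulva, bladder, urethra, or prostate" and an "Eastern Cooperative Oncology Group performance score of 0–2". The listed eligibility criteria set no limit on stage.

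The article does not mention death as an event, a competing risk, cumulative incidence, or a rule for censoring at death.

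**The concern.** Incidence is the share of randomized patients who actually develop chronic RIE. A patient who dies free of it cannot develop it later, so death is a competing event. The planned event is toxicity, not toxicity or death, so in a Kaplan-Meier analysis a patient who dies without it leaves the risk set as censored. The curve then treats that patient as if he or she had the same future risk as those still alive. One minus the curve is the risk in a hypothetical population in which nobody dies, which is not the quantity that the aim names.

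What is at stake is the chronic RIE percentage reported for each arm, and the absolute difference between arms derived from it.

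**Working it through.** **Inputs.** From the article: the Kaplan-Meier method, a toxicity-only event and a 5-year horizon. The article gives no chronic RIE rate, no mortality and no power for the chronic endpoint, so there is no figure of its own to reproduce here. Its sample size of 118 per group concerns acute toxicity (30% against 15%) and has no bearing on this point. The following are therefore my assumptions:
- one minus Kaplan-Meier (1−KM) at 5 years of 30%;
- 5-year mortality of 5% to 40%, meaning the risk from the death hazard taken alone;
- constant hazards of chronic RIE and death, acting independently.

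**Formulas.** With 5-year Kaplan-Meier risk k and mortality d:
- chronic RIE hazard: a = −ln(1−k)/5;
- death hazard: b = −ln(1−d)/5;
- cumulative incidence at 5 years: a/(a+b) × [1 − exp(−5(a+b))].

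**Worked case, k = 30%, d = 30%.** Here a = b = 0.0713 per year. The cumulative incidence is 0.5 × [1 − 0.7 × 0.7] = 0.5 × 0.51 = 25.5%. The Kaplan-Meier figure is 30.0%, an excess of 4.5 points. A simulation of 400,000 patients with these hazards gave 25.5% with chronic RIE before death.

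**Range, k = 30%.**

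| Assumed 5-year mortality | Cumulative incidence | Excess of 1−KM (points) | Ratio of 1−KM to incidence |
|---|---|---|---|
| 5% | 29.3% | 0.7 | 1.02 |
| 10% | 28.6% | 1.4 | 1.05 |
| 20% | 27.1% | 2.9 | 1.11 |
| 30% | 25.5% | 4.5 | 1.18 |
| 40% | 23.8% | 6.2 | 1.26 |

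With no deaths the excess is zero. Over the same mortality range it is 0.3 to 2.1 points if k is 10%, and 0.9 to 8.0 points if k is 40%.

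**Sensitivity to timing.** Suppose the same 30% all arises in the first 2 years, with death still constant over 5 years. Then a = −ln(0.7)/2 = 0.178 per year, and the incidence is a/(a+b) × [1 − exp(−2(a+b))]. This gives 28.8%, 28.1% and 27.3% at mortality of 20%, 30% and 40%. The excess falls to 1.2, 1.9 and 2.7 points, a little over 40% of the constant-hazard figures.

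**Comparison of arms, equal survival.** Take Kaplan-Meier risks of 30% and 15%, with 30% mortality in both arms. The cumulative incidences are 25.5% and 12.7%. The absolute difference falls from 15.0 to 12.8 points. The ratio is 2.00 on the Kaplan-Meier scale and 2.01 on the incidence scale; across mortality of 5% to 40% it stays between 2.00 and 2.02.

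**The case against.** The strongest reply has four parts.

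1. **Nothing says that deaths are censored or that 1−KM will be reported as incidence.** The article speaks of times to toxicity and of comparing curves, and a condensed article may leave the handling of death to the full protocol or analysis plan. This is correct as to wording. But the method and the event are both stated. With a toxicity-only event, Kaplan-Meier offers no other place for a death free of toxicity than censoring, and it is the only estimator named for an aim expressed as incidence. The mismatch lies in what is written.

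2. **The size is assumed throughout.** This stands in full. A reader might infer that many patients will die first and that the bias is known to be large. The article gives no mortality, no chronic RIE rate and no timing of events, and at 5% to 10% mortality the excess is only 0.7 to 1.4 points in the main illustration.

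3. **The log-rank comparison is sound.** This also stands. A reader might infer that the planned log-rank test and Cox model are wrong. They are not: with deaths censored they compare the cause-specific hazard of chronic toxicity, which is a fair way to ask whether probiotics act on it. Gray's test answers a different question, because it also picks up any effect on mortality; replacing the log-rank test with it would be a preference.

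4. **There is no reason to expect a survival difference between arms.** The article indeed gives none. A reader might infer that the absolute difference is therefore safe. It is not, because it shrinks even with equal survival. The relative effect, by contrast, hardly moves.

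**Conclusion.** The point holds for the estimate of incidence. The estimator named for chronic toxicity does not match the secondary aim, and 1−KM read as incidence is too high whenever patients die free of chronic RIE while others still go on to develop it. The direction is certain under that condition.

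The size cannot be derived from the article. The illustrations run from under 1 point at 5% mortality to about 6 points at 40%, for an assumed Kaplan-Meier risk of 30%, independent causes and constant hazards; early chronic RIE more than halves them. Absolute differences between arms are overstated as well, and relative effects are practically unchanged.

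The point is limited to a secondary endpoint. The planned hazard comparisons are valid as they stand, and the primary comparison of acute RIE by Chi-Square or Fisher's exact test is not affected.

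**What to change.** - Estimate chronic RIE in each arm by the cumulative incidence function (Aalen-Johansen), with death as a competing event, and take the reported percentages and absolute difference from it.
- Keep the planned log-rank test and Cox model for chronic RIE, state that deaths free of chronic RIE are censored in them, and label them as comparisons of the cause-specific hazard. Gray's test may be added but is not needed.
- Record the date of death at the planned follow-up visits.

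**Cost.** A few lines of analysis text, with no extra patients, no extra visits and no change to the primary analysis. The one practical condition is the date of death: the article says that data on endpoints are collected and does not list death among them, so its availability is likely but not stated, and should be confirmed.
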